## 2.2 Hypothesis

Previous studies have demonstrated that a 3 week interval between homologous MVA85A–MVA85A administered systemically does not enhance responses (8). We hypothesise that responses will be boosted in the aerosol–systemic and systemic-aerosol group but not in the systemic–systemic group.

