# **9. STATISTICS**

## **9.1 Statistics**

This is primarily a trial with descriptive endpoints. Twelve subjects will be recruited into each arm of the trial (i.e. 36 in total). Our previous experience with clinical trials using MVA85A over the last 10 years suggests that this sample size is a feasible number to recruit, screen, enroll, and follow up in practical terms, whilst also allowing the determination of any substantial and clinically significant differences in safety and cell-mediated immunity between the three groups. A twofold increase in the magnitude of the cellular immune response (as measured by Elispot response to 85A peptide stimulation) is considered immunologically meaningful. Extrapolating effect size and variability from the completed initial aerosol vaccine safety study (TB026), twelve volunteers are needed to have 80% power to detect an immunologically meaningful difference in the summed peptide pools and 8

volunteers to achieve the same for single peptide pool of 85A. This sample size is appropriate for a proof-of-concept Phase I safety study.

It is anticipated that the immunological endpoints will not follow a normal distribution. A log transformation will be applied and if the resulting data are normally distributed they will be summarised by group using means and standard deviations. The one-week and six-month responses will be compared between the three groups using a t-test. If the resulting data are not normally distributed then medians and interquartile ranges will be used to summarise the data and the Mann Whitney U test will be used for statistical comparisons. An area-under-curve analysis will be used to compare the overall responses over time between the three groups. This analysis will make use of data collected at all time points.

Differences between means or medians between the three groups will be presented along with their 95% confidence intervals. Within each group, paired data will be analysed using either a paired t-test or the Wilcoxon matched pairs test depending on the normality of the data.

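### Protocol 9.1 fixes a two-sample test for a three-arm comparison and names no pair and no global test: about 12% false positives per analysis at an assumed 5% level, and roughly 18–32% for one endpoint over its three analyses

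*Protocol*

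**What the plan says.** Section 9.1 opens with "This is primarily a trial with descriptive endpoints" and plans 12 subjects in each of three arms. It then commits to tests on the immunological endpoints: "The one-week and six-month responses will be compared between the three groups using a t-test". If the log-transformed data are not normal, "the Mann Whitney U test will be used for statistical comparisons". It adds: "An area-under-curve analysis will be used to compare the overall responses over time between the three groups". Results are to be shown as follows: "Differences between means or medians between the three groups will be presented along with their 95% confidence intervals". On sample size it says that "twelve volunteers are needed to have 80% power to detect an immunologically meaningful difference in the summed peptide pools", taking a twofold change in the 85A ELISPOT response as meaningful.

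The section names no pair of arms and no three-group test, and it does not say which one-week visit is meant. Section 2.2 has a directional hypothesis: "We hypothesise that responses will be boosted in the aerosol–systemic and systemic-aerosol group but not in the systemic–systemic group". Section 9.1 links no comparison to it. Section 3 makes safety the primary objective and immunogenicity secondary.

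**The concern.** A t-test or a Mann-Whitney test compares two groups. Applied to three, it becomes either three pairwise tests or a selection that the protocol does not specify. An analysis plan that follows this wording inherits the problem, because the choice of test is stated here and not left open.

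Two features of the design make the gap matter more:

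- **One-week is ambiguous.** Table 1 has a visit one week after the prime (day 7) and one week after the boost (day 35). Under the regimens in section 6.1, Groups 2 and 3 receive identical treatment until day 28. If day 7 is meant, a significant difference between Groups 2 and 3 cannot be a regimen effect.
- **Group 2 is mixed after day 28.** Under section 4.1, Group 2 volunteers due their boost on or after 2 September 2015 receive placebo by both routes. Day 35, six months and AUC all take in post-boost data, and section 9.1 does not say how these volunteers enter the comparison.

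At stake is whether a reported difference between routes or regimens in the immunology can be told apart from one thrown up by repeated testing.

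**Working it through.** **Inputs.** Three arms of 12, a twofold difference (0.301 on the log10 scale), 80% power and the analyses at one week, six months and AUC come from section 9.1. The two-sided 5% level is an assumption, inferred from the 95% confidence intervals. The protocol gives no SD, and the correlation between analyses is not stated, so it is varied.

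**The protocol's own figure.** Without an SD, the 12 volunteers can be neither confirmed nor refuted; only the implied SD can be solved for.

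- Two-sample t-test, 12 per group, 80% power: standardised difference d = 1.197, so SD = 0.301 / 1.197 ≈ 0.25 log10.
- Paired test with 12 subjects: d = 0.889, so SD = 0.301 / 0.889 ≈ 0.34 log10.

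Section 9.1 does not say which of the two was used.

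**One endpoint, one analysis, no true difference.** The probability that at least one of three pairwise tests has p < 0.05:

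- Pooled variance: P(Q > √2 × t(0.975; 33 df)), with Q the studentized range for 3 groups and 33 df, is 0.120.
- Simulated two-sample t-tests: 12.0–12.5%. Mann-Whitney: 10.7%.
- For reference, three independent tests would give 1 − 0.95³ = 14.3%.

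This is about 2.4 times the nominal 5% (0.12 / 0.05). It needs no assumption about SD or correlation between analyses.

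**One endpoint, three analyses (nine tests), no true difference.** Two simulations were run: one with three equally correlated readouts, one with the AUC built from the ten visits from day 0 to day 168.

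| Correlation | Three equicorrelated readouts | One week, six months, AUC from visits |
|---|---|---|
| 0 | 32.0% | 31.1% |
| 0.3 | 31.1% | 28.2% |
| 0.5 | 28.8% | 25.9% |
| 0.8 | 22.9% | 20.9% |
| 0.9 | not run | 18.0% |

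The range is therefore roughly 18–32%. Nine independent tests would give 1 − 0.95⁹ = 37%, but the three pairs share arms and the AUC contains the other two time points.

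**Effect of a global test first.** With exactly three groups, if the global null is false then at most one pairwise null can still be true. Testing pairs at 5% only after a significant global test therefore needs no splitting of alpha. Simulated rate for one analysis: 4.9% with ANOVA, 4.8% with Kruskal-Wallis.

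**Cost in power** for the pair that truly differs by d = 1.197:

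| Pattern of the three means | As written | Global test first | Bonferroni over 3 pairs |
|---|---|---|---|
| d, d, 0 | 80% | 76% | 63% |
| d, 0, 0 | 80% | 77% | 64% |
| d, d/2, 0 | 80% | 70% | 64% |

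The loss is 3–4 points in the first two patterns and 10 in the third. Bonferroni would need 17 per arm to restore 80%.

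**The case against.** The strongest reply is that this is a small Phase I safety trial. Section 9.1 calls its endpoints primarily descriptive, the primary endpoint is adverse events, and the trial summary and Table 1 label the blood immunology sampling exploratory. Alpha, multiplicity rules and contrasts are commonly left to a statistical analysis plan, and one may exist. Most of this stands. Silence on adjustment is not a finding, and the point rests only on the stated choice of a two-group test for three groups. The exploratory label attaches to samples, though, not to tests, and the same section commits to significance tests and a power claim.

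Three stronger readings are tempting, but the documents do not support them:

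- A reader might infer an overall false-positive rate of at least 29%. That figure belongs to three readouts at a correlation near 0.5. With the AUC built from the visits, one endpoint gives 25.9% at that correlation and 18.0% at 0.9. A rate over all endpoints needs a count of readouts and correlations that the protocol does not give.
- A reader might infer that the 80% power fails because both Groups 1 and 2 must exceed Group 3. Section 2.2 sets no such criterion. It reads at least as naturally as a change within each group after the boost, for which section 9.1 provides paired tests. After the section 4.1 amendment, 12 aerosol-boosted Group 2 volunteers cannot be assumed either.
- A reader might infer a loss of confirmatory error control. The trial makes no confirmatory immunology claim.

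**Conclusion.** The point holds in limited form. Section 9.1 prescribes a two-sample test for a three-arm comparison without naming a pair or a global test. Followed as three pairwise tests, it gives about 12% false positives per analysis, and roughly 18–32% for one endpoint over one week, six months and AUC. The 12% rests on the inferred two-sided 5% level and 12 per arm; the wider range also rests on assumed correlations. The power costs of the remedy rest on an effect size back-solved from the stated 80%, taken as a between-group figure. The consequence is weaker interpretation of secondary immunology results. It should be corrected because the correction is short and cheap, but it does not threaten the primary safety objective.

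**What to change.** In section 9.1, replace the t-test sentence with wording such as: *The three groups will be compared by one-way ANOVA on the log scale (Kruskal-Wallis if not normal). Pairwise comparisons will be tested at two-sided 5% only if the global test is significant at 5%; after ANOVA they will use the pooled variance.*

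Also:

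- Name the summed-pool 85A ELISPOT, on which the 12 per arm was based, as the key immunological endpoint.
- State whether one-week means day 7 or day 35, noting that Groups 2 and 3 are treated identically up to day 28.
- Say how Group 2 volunteers given placebo at day 28 enter any post-boost comparison, including six months and AUC.
- Label the other readouts and time points exploratory, reported with estimates and unadjusted 95% confidence intervals.
- If the 80% is a between-group figure, say that it refers to one pairwise comparison, and that it is about 76–77% with the global test first in the main patterns.

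A fixed testing order across the three analyses is not advised. If stopping depended only on the global test, a true null pair (Group 2 against Group 3, with Group 1 different) could be tested at 5% up to three times. A simulation of that case gave a false claim in 10.9% of trials at correlation 0.5.

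The cost is a few sentences and no extra volunteers, visits or assays. Pairwise power falls by about 3–4 points, up to about 10 in the midway pattern, and readouts labelled exploratory can no longer be presented as significant findings.

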### Anti-vaccinia Ig-G levels (arbitrary U/ml) measured in serum samples Vaccination group median (+/- SD)

[figure not shown]

**Figure 2:** Vector specific IgG response induced by vaccination with MVA85A measured by ELISA. The plot shows the median change from prevaccination level for the BCG prime with MVA85A intradermal boost group with the closed circles and for the BCG prime with MVA85A aerosol boost group with triangles. Error bars are standard deviations from the median (35).

This effect of reducing anti-vector responses by mucosal administration has also been demonstrated in mice, rabbits and guinea pigs (12, 36, 37). There is an increased need to find strategies to overcome anti-vector immunity in vaccine development especially for vaccines that will need to be given repeatedly (e.g. seasonal influenza), so if this is also demonstrated in humans, this would be an important development for the field of viral vaccines and respiratory pathogens for which mucosal immunisation may improve efficacy (11, 12).

This project will quantify for the first time the induction of anti-vector immunity (humoral and cell-mediated) by both aerosol and systemic administration of MVA85A. The functional relevance of this anti-vector immunity will be evaluated by a second boost vaccination of MVA85A via a different administration route, one month after the first, priming immunisation. This data will have implications for the TB vaccine field but also for the wider vaccine community and for the development of mucosal vaccination strategies for other respiratory and mucosal pathogens.

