| Secondary Objectives
To characterise mucosal and systemic immunogenicity of viral vector (MVA) and insert (Ag85A) by comprehensive characterisation of humoral and cellular immune responses

Evaluate functional relevance of anti-vector immunity induced by aerosol and systemic immunisation in MVA85A-prime followed by homologous MVA85A-boost administered 4 weeks after the MVA85A-prime | 

1. Induction of humoral and cell-mediated immunity to MVA by aerosol and systemic immunisation

2. Induction of cell-mediated and humoral immunity to Ag85A by aerosol and systemic immunisation

3. Effect of a boosting immunisation one month after prime on humoral and cell-mediated immunity to insert (Ag85A) and vector (MVA)

 |

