#### **\* Change to Group 2 vaccinations**

A change has been made for group 2 volunteers due to receive their day 28 boost vaccination on or after 2 September 2015, due to a higher frequency of mild respiratory adverse events in this group. Local (skin) and systemic symptoms were as expected and consistent with data from previous studies. These volunteers will not receive the day 28 boost vaccination, but instead will receive a placebo by both intradermal and aerosol inhaled routes to maintain blinding. Additional safety and immunological information will be gained by continuing with day 35 bronchoscopy in these volunteers. Any volunteer not wishing to proceed in this manner will remain in follow up with no vaccination or bronchoscopy.

As BCG is protective in childhood, it is routinely given at birth in TB endemic countries but is also in widespread use in children and adolescents in much of the rest of the world. Therefore, as in previous trials of intradermal MVA85A, we propose to vaccinate BCG-primed subjects. These will be healthy men and women aged 18-55 years who have been previously vaccinated with BCG.

All subjects will have received BCG vaccination at least six months prior to enrolment. MVA85A ( $5 \times 10^7$  pfu) or saline placebo will be administered by systemic (intradermal) or aerosol (Omron jet nebuliser) route (paired placebo design). The interval between the two vaccinations is one month.

In order to minimise the risk from bronchoscopy, subjects with a history or evidence of lung disease will be excluded. This will be determined by our standard screening procedures (history, examination, urine analysis, and blood tests), and, in addition, a chest x ray and pulmonary function testing.

The peak effector T-cell response in blood is ~7 days post-vaccination with MVA85A. Pulmonary mucosal responses are expected to follow a similar time course and a preclinical study has demonstrated this in non-human primates (35). Thus bronchoscopy and bronchialveolar lavage will be performed seven days after each vaccination.

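### The time-point group comparisons in 9.1 are set at one week and six months, and on the Table 1 reading neither tests the boosting hypothesis near the expected post-boost peak at day 35

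*Protocol*

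**What the plan says.** **The question.** Section 2.2 states: "We hypothesise that responses will be boosted in the aerosol–systemic and systemic-aerosol group but not in the systemic–systemic group". Section 2.1 says of the vector response: "The functional relevance of this anti-vector immunity will be evaluated by a second boost vaccination of MVA85A via a different administration route". The third secondary endpoint in section 3 is the effect of the boost on immunity to insert and vector.

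**When the response is expected.** Section 4.1 states: "The peak effector T-cell response in blood is ~7 days post-vaccination with MVA85A". With a boost on day 28, that points to day 35.

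**The planned analysis (9.1).**
- Time-point comparison between groups: "The one-week and six-month responses will be compared between the three groups using a t-test", with Mann-Whitney as the alternative if the logged data are not normal.
- AUC: "An area-under-curve analysis will be used to compare the overall responses over time between the three groups". The text adds: "This analysis will make use of data collected at all time points".
- Within groups: "Within each group, paired data will be analysed using either a paired t-test or the Wilcoxon matched pairs test". No time points are named for these.
- Differences between groups are to be given with 95% confidence intervals.

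**The clock.** Table 1 labels day 7 as week 1, day 28 as week 4, day 35 as week 5 and day 168 as week 24. Section 4.3 counts the 24 weeks from enrolment and describes the same period as five months from the last vaccination.

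**The concern.** The boosting hypothesis is a statement about differences between groups in what happens after day 28. The two time points named for comparing groups appear to fall on either side of that response: one before the boost, the other long after it.

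At day 7, Groups 2 and 3 have had the same treatment (section 6.1, Trial regimen), so that contrast has no expected difference and says nothing about boosting. If the only analysis that isolates the day 28 to day 35 increment is a separate paired test in each group, the three-way statement in 2.2 may end up resting on a comparison of p-values. One group can then be significant and another not, without evidence that the two differ.

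**Working it through.** **1. The plan's own figure.** Section 9.1 gives 12 volunteers for 80% power to detect a twofold difference in summed pools. It states no SD, alpha, sidedness, test or time point, so the figure cannot be reproduced forwards. Solving backwards with delta = log10(2) = 0.301 and an assumed two-sided alpha of 0.05:
- two-sample t-test, 12 per arm: log10 SD = 0.252;
- paired t-test, 12 volunteers: SD of the log10 change = 0.339.

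These values are circular. They serve below only as a plausible scale, not as a check of the sample size.

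**2. Timing of the named tests.**
- One week on the Table 1 labels: day 7, and 28 − 7 = 21 days before the boost.
- Six months: day 168, and 168 − 28 = 140 days (20 weeks) after the boost.
- Expected post-boost peak: 28 + 7 = day 35, which is week 5.

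Six months matches week 24 counted from enrolment. The same clock makes one week day 7.

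**3. What the AUC can see.** Trapezoid weights on the Table 1 days, each visit taking half of each adjoining interval:

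| Day | 0 | 2 | 7 | 14 | 28 | 30 | 35 | 42 | 84 | 168 |
|---|---|---|---|---|---|---|---|---|---|---|
| Weight (of 168) | 1 | 3.5 | 6 | 10.5 | 8 | 3.5 | 6 | 24.5 | 63 | 42 |

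- Days 30 to 168: 3.5 + 6 + 24.5 + 63 + 42 = 139, and 139/168 = 83%.
- Day 35 alone: 6/168 = 3.6%.
- Days 84 and 168: 105/168 = 62.5%.

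Illustration: one group has twice the response of a flat comparator at the visits shown, so AUC ratio = 1 + (sum of those weights)/168. Power is for a two-sample t-test with 12 per arm, two-sided 0.05, and noncentrality log10(ratio)/(0.252·√(2/12)). It assumes that log10 AUC has the back-solved SD of 0.252.

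| Twofold difference at | AUC ratio | Power |
|---|---|---|
| Day 35 only | 1 + 6/168 = 1.04 | about 5% |
| Days 35, 42 | 1 + 30.5/168 = 1.18 | about 10% |
| Days 35 to 84 | 1 + 93.5/168 = 1.56 | about 43% |
| Days 35 to 168 | 1 + 135.5/168 = 1.81 | about 67% |

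A direct day 35 comparison has 80% power on the same assumption, because the SD was solved to give that.

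**4. What separate paired tests can show.** Paired t-test, 12 volunteers, two-sided 0.05, assumed SD of the log10 change 0.25, 0.30 and 0.34:
- a true 1.5-fold boost is non-significant 40%, 54% and 63% of the time;
- a true twofold boost, the protocol's own threshold, is non-significant 3%, 12% and 20% of the time.

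Suppose Groups 1 and 3 have the same true boost. The chance that Group 1 is significant and Group 3 is not is p(1 − p), where p is the power:
- 1.5-fold: 0.604 × 0.396 = 0.24; 0.458 × 0.542 = 0.25; 0.374 × 0.626 = 0.23.
- Twofold: from 0.966 × 0.034 = 0.03 (SD 0.25) to 0.797 × 0.203 = 0.16 (SD 0.34).

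The pattern described in 2.2 can therefore appear between groups that do not differ.

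**The case against.** **The one-week anchor is not stated.** Table 3 and section 4.1 place a bronchoscopy one week after both prime and boost, so one week after each vaccination is a possible reading of 9.1. On that reading a day 35 comparison is already planned. For Group 2 v Group 3, which share the same prime, it would carry no prime-route difference. This stands. The Table 1 reading is the more natural one but remains an inference, and the ambiguity itself needs settling.

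**The day 7 test has a purpose.** A reader might infer that 2.2 is the only hypothesis and that a pre-boost test is wasted. It is not: section 2.1 also hypothesises that mucosal immunisation does not induce systemic anti-vector immunity, and secondary endpoints 1 and 2 concern induction by route. Group 1 against Groups 2 and 3 before the boost serves that question.

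**The AUC covers the boost.** A reader might infer that no between-group analysis touches the post-boost response. The 83% weight shows otherwise. A sustained boost would enter the AUC comparison, and only a brief peak is largely lost.

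**No rule equates non-significance with no boost.** A reader might infer that the plan would declare Group 3 not boosted from a non-significant paired test. Section 9.1 states no such rule and calls the endpoints primarily descriptive. The calculation in step 4 shows a risk of misreading, not an error in the text. Its larger figures use an effect below the protocol's twofold threshold.

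**A statistical analysis plan may settle this.** It may, but the protocol itself names the time points, and on the Table 1 labels they miss the day 35 response.

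**Conclusion.** The point holds in a limited form. Read with Table 1, section 9.1 names no time-point comparison between groups that addresses the boosting hypothesis or the third secondary endpoint near day 35. The AUC is a partial substitute: adequate for a difference that lasts for months, close to blind to one confined to day 35 (ratio 1.04, power about 5%). Within-group tests do not fill the gap, because they do not compare groups.

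The timing and weight figures follow from Table 1 alone. The power and miss rates rest on assumed SDs (0.252 for log10 AUC, 0.25 to 0.34 for the log10 change) and two-sided 0.05, none of which the protocol gives.

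Severity is moderate. The primary objective is safety, the trial is mainly descriptive, and the samples needed are already in the schedule.

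**What to change.** In section 9.1:

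1. State the anchor of the one-week response. Keep the day 7 comparison and label it as the prime-route question.
2. Add a named between-group comparison of the boost: the log10 change from day 28 to day 35, Group 1 v Group 3 and aerosol-boosted Group 2 v Group 3, each back-transformed to a fold ratio with 95% CI.
3. For Group 2 v Group 3, where the prime is identical, a day 35 comparison adjusted for day 28 is also sound. It is debatable for Group 1 v Group 3, because day 28 follows randomisation and depends on the prime route.
4. Report each group's day 35/day 28 ratio with 95% CI against the twofold threshold. Do not infer an absent boost from a non-significant p-value.
5. Report a post-boost AUC (days 28 to 168, day 28 value subtracted) beside the overall AUC.

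**Cost.** Wording only, since blood is already drawn at days 28 and 35, and one more secondary comparison. Expected precision: the 95% limits are the ratio multiplied and divided by 10^(t·SD·√(1/n1 + 1/n2)). With 12 v 12 (t = 2.074) and SD of change 0.25 to 0.34, that factor is 1.63 to 1.94.

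After the amendment in section 4.1, the aerosol-boosted part of Group 2 is a smaller subset defined by calendar date, and its size is not given. If it were 6, purely as an assumption (t = 2.120), the factor would be 1.84 to 2.29. That contrast should be labelled as less precise and as based on a calendar-defined subset.

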| Physical examination                            | X  |     |     | X    |     |     |     | X    |     |     |     |
| Vital signs                                     | X  | X   | X   | X    | X   | X   | X   | X    | X   | X   | X   |
| Urinalysis                                      | X  |     |     |      |     |     |     |      |     |     |     |
| Chest x ray                                     | X  |     |     |      |     |     |     |      |     |     |     |
| Pulmonary function tests                        | X  | X   | X   | X    |     | X   | X   | X    |     |     |     |
| β-HCG urine test                                | X  | X   |     | X    |     | X   |     | X    |     |     |     |
| Vaccinations                                    |    | X   |     |      |     | X   |     |      |     |     |     |
| Bronchoscopy                                    |    |     |     | X    |     |     |     | X    |     |     |     |
| Local & systemic events/reactions               |    | X   | X   | X    | X   | X   | X   | X    | X   | X   | X   |
| Diary cards provided                            |    | X   |     |      |     | X   |     |      |     |     |     |
| Diary cards collected                           |    |     |     |      | X   |     |     |      | X   |     |     |
| Biochemistry (4mL)***                           | X  |     | X   | X    |     |     | X   | X    |     |     |     |
| Haematology (2mL)****                           | X  |     |     | X    |     |     |     | X    |     |     |     |
| Coagulation (4mL)                               | X  |     |     |      |     |     |     |      |     |     |     |
| HBV, HCV, HIV (10mL)                            | X  |     |     |      |     |     |     |      |     |     |     |
| HLA typing (4mL)                                |    | X   |     |      |     |     |     |      |     |     |     |
| Exploratory immunology incl ELISPOT (20-60mL)** | X  | X   | X   | X    | X   | X   | X   | X    | X   | X   | X   |
| Blood vol (mL)                                  | 50 | 64  | 20  | 66   | 60  | 60  | 20  | 66   | 60  | 60  | 60  |
| Cumulative blood vol (mL)                       | 50 | 114 | 134 | 200  | 260 | 320 | 340 | 406  | 466 | 526 | 586 |

|      |                                                                                                                                                              |

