## 4.2 Randomisation

In order to reduce bias and the influence of any difference in the baseline characteristics between the three groups, we have chosen to randomise the allocation of subjects. This aims to achieve a balance between the three groups in any important confounding factors such as levels of pre-existing antimycobacterial immunity (influenced by, for example, country of origin and length of time elapsed since prior BCG vaccination). This will be performed by variable block randomisation using sequentially numbered sealed envelopes, prepared by an independent colleague at the Centre for Statistics in Medicine, to ensure allocation concealment. Volunteers are blinded as they will receive a paired placebo at the same time of vaccination. The bronchoscopist will be blinded to the route of vaccine administration. This is intended to eliminate any bias in the reporting of the appearance of the lung mucosa and extent of airway inflammation. In addition, the postdoctoral researcher in the laboratory overseeing the immunological analyses will also be blinded to reduce any bias that could be introduced at the sample processing stage. All samples will be anonymised.

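### The one-week and six-month between-group tests on log responses make no adjustment for the day 0 ELISPOT, although the protocol names pre-existing immunity as an important confounder and measures it.

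*Protocol*

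**What the plan says.** Protocol section 9.1 fixes the scale first: "A log transformation will be applied and if the resulting data are normally distributed they will be summarised by group using means and standard deviations". It then fixes the test: "The one-week and six-month responses will be compared between the three groups using a t-test". If the logged data are not normal, the Mann-Whitney U test replaces it. No covariate or change score is named for these contrasts. The same section adds a between-group area-under-curve analysis that uses every time point, and paired tests within each group.

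Section 4.2 gives the purpose of randomisation: "This aims to achieve a balance between the three groups in any important confounding factors such as levels of pre-existing antimycobacterial immunity". The means is stated as: "This will be performed by variable block randomisation using sequentially numbered sealed envelopes". No stratification factor is named.

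Table 1 (section 1) marks immunology blood including ELISPOT at screening, at day 0 and at every later visit. Bronchoscopy is marked only at days 7 and 35, so lavage has no pre-vaccination value.

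On sample size, section 9.1 plans 12 per arm and states: "A twofold increase in the magnitude of the cellular immune response (as measured by Elispot response to 85A peptide stimulation) is considered immunologically meaningful". It claims 80% power with 12 volunteers for the summed peptide pools and with 8 for a single pool.

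**The concern.** All volunteers have had BCG, so they arrive with differing responses to mycobacterial antigens, Ag85A among them. The protocol treats this as important enough to justify randomising, and it collects a direct pre-vaccination measure. That measure is then left out of the between-group contrasts at one week and six months.

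Two things are at stake. First, with 12 per arm a chance baseline difference of appreciable size is common, and for the particular sample drawn the unadjusted contrast carries part of it. Second, any outcome variance that day 0 explains stays in the error term and widens the interval. How much depends on the correlation between day 0 and post-vaccination values, which the protocol does not give.

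**Working it through.** **Inputs.** From section 9.1: 12 per arm, three arms, a twofold difference (log10 2 = 0.301), 80% power, 95% intervals. Not in the protocol: the SD, alpha, sidedness, the test behind the sample size, and the correlation r between log day 0 and log post-vaccination response. I assume two-sided 0.05 and show a range for r.

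**The stated sample size.** It cannot be reproduced without an SD, so I solved for the log10 SD that gives 80% power at a twofold difference:

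| Assumed test | n = 12 | n = 8 |
|---|---|---|
| Two-sample t, two-sided | 0.252 | 0.200 |
| Normal approximation, two-sided | 0.263 | 0.215 |
| Normal approximation, one-sided | 0.297 | 0.242 |
| Paired t, two-sided | 0.339 | 0.260 |

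I use 0.2515 (two-sample t, n = 12), since section 9.1 fixes a t-test between groups. The standardised effect is 0.301/0.2515 = 1.197.

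**Chance imbalance.** The baseline mean difference between two arms of 12 has standard error √(2/12) = 0.408 SD. So P(|difference| > 0.5 SD) = P(|Z| > 0.5/0.408) = P(|Z| > 1.225) = 22%.

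**Carry-over.** A baseline difference of 0.5 SD shifts the log10 contrast by r × 0.5 × 0.2515:

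- r = 0.3: 0.038, or 1.09-fold
- r = 0.5: 0.063, or 1.16-fold
- r = 0.7: 0.088, or 1.22-fold

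At the largest SD in the table, 0.339, the shifts would be 1.12-, 1.22- and 1.31-fold.

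**One three-group ANCOVA.** Error degrees of freedom are 36 − 3 − 1 = 32. The variance relative to the unadjusted contrast is (1 − r²)(1 + 1/31), where the second factor is the average cost of estimating the slope. The interval-width ratio is t(0.975, 32) × √[(1 − r²)(1 + 1/31)] / t(0.975, 22), with t values 2.037 and 2.074. Power uses the noncentral t with noncentrality 2.932/√[(1 − r²)(1 + 1/31)], where 2.932 = 1.197/0.408.

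**Separate pairwise ANCOVAs.** Error degrees of freedom are 24 − 2 − 1 = 21 and the variance factor is (1 − r²)(1 + 1/20).

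| r | Power, three-group | Interval width | Power, pairwise | Interval width |
|---|---|---|---|---|
| 0 | 79.9% | unchanged | 77.9% | 2.8% wider |
| 0.3 | 83.5% | 5% narrower | 81.6% | 2% narrower |
| 0.5 | 89.8% | 14% narrower | 88.3% | 11% narrower |
| 0.7 | 97.5% | 29% narrower | 96.8% | 27% narrower |

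Simulation with 20,000 runs per setting agreed within about half a percentage point for both forms. The pairwise version breaks even on interval width at r of about 0.23 and loses slightly below that.

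**Source of the three-group gain.** A three-group model without the covariate has 33 error degrees of freedom and gives 81.2% power, with an interval 1.9% narrower (2.035/2.074 = 0.981). That part comes from pooling the error variance and assumes a common variance. The rest is due to day 0.

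**The case against.** The strongest case against is that nothing in section 9.1 is false. A t-test after randomisation is valid, and its interval already allows for chance imbalance. Randomising to balance a factor and then testing without adjustment is not a contradiction. Covariate adjustment is often settled in a statistical analysis plan, and one not shown here might add it. The trial is mainly descriptive, its primary endpoint is safety, and a 1.16-fold shift is small beside the twofold difference called meaningful. The correlation is unknown, and pairwise adjustment costs a little precision if it is low.

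Most of this stands and limits the point. It does not remove it, because the protocol does not leave the method open: it names a test without the baseline value. Fitted as one three-group model, adjustment costs essentially nothing relative to the planned t-test even at zero correlation.

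A reader might infer more than the documents support:

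- **That the planned test is biased or invalid.** It is unbiased over randomisation. The imbalance matters conditionally, for the sample drawn.
- **That responses are compared untransformed.** Section 9.1 logs them first.
- **That day 0 is ignored throughout.** The area-under-curve analysis and the paired tests can use it, though neither adjusts the one-week or six-month contrast.
- **That section 4.2 names the day 0 assay value.** It names pre-existing antimycobacterial immunity. The day 0 Ag85A ELISPOT is a measure of that.
- **That section 4.2 also calls for adjusting anti-MVA responses.** Its wording is about antimycobacterial immunity, and section 5.2 excludes earlier recombinant MVA vaccination.

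**Conclusion.** The point holds as a worthwhile improvement to a secondary comparison. The fixed between-group tests leave out a baseline value that the protocol's own reasoning marks as important and that Table 1 already collects. The 22% chance of an imbalance above 0.5 SD between two given arms rests only on 12 per arm and a roughly normal distribution of baseline means.

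The fold shifts and power figures rest on further assumptions: a log10 SD of 0.25 back-solved from the power statement, two-sided 0.05, an assumed correlation, common variance, and 12 analysable volunteers in each arm. The gain is negligible at zero correlation, modest at 0.3 and substantial at 0.5 or above. It may differ between one week and six months. It cannot be said that precision is certainly being lost, since the documents give no correlation.

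**What to change.** In section 9.1, for the blood Ag85A ELISPOT comparisons, replace the two-sample t-test at each time point by one ANCOVA fitted to all three groups. The outcome is the log response and the covariate is the log day 0 value of the same assay. Report the adjusted fold ratios between groups with 95% confidence intervals. If residuals are clearly non-normal, use rank ANCOVA in place of Mann-Whitney.

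Specify the three-group fit explicitly, because separate pairwise fits gain less. Lavage outcomes have no day 0 sample and stay unadjusted. Adjusting anti-MVA responses is optional.

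The cost is a change of wording and one degree of freedom. No new sample, visit or volunteer is needed.
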